## Abstract

**Background:**

Long COVID (postacute sequelae of SARS-CoV-2 infection) is a heterogeneous condition with persistent multisystem symptoms and substantial functional burden. Integrative longitudinal studies combining clinical phenotyping, lifestyle factors, and immunobiological markers are needed to clarify determinants of symptom persistence and inform risk stratification and targeted interventions.

**Objective:**

This study aims to identify clinical, biological/immunological, and sociodemographic factors associated with Long COVID status by comparing individuals with persistent symptoms to matched recovered controls, and to evaluate longitudinal changes in symptoms and secondary outcomes over follow-up.

**Methods:**

ARALongCOV is a longitudinal matched case-control observational study conducted in Aragón, Spain, including adults (≥18 years of age) with confirmed SARS-CoV-2 infection. Participants are recruited through 3 sources: the Long COVID Aragón Patient Association, the Aragón Health Service database, and primary care consultations. Long COVID and recovered participants are individually matched 1:1 (without replacement) on sex/gender (exact), age (±3 years), and date of acute COVID-19 diagnosis (±30 days). Outcomes include persistent symptoms and functioning and patient-reported outcomes (quality of life, physical activity, diet, sleep, mental health, functional status, cognitive performance, pain catastrophizing, and fatigue), alongside clinical variables and biochemical/immunological markers (including inflammatory and cytokine profiles, SARS-CoV-2 antispike immunoglobulin G serology, and viral reactivation serologies). Measurements are obtained at baseline (T0) and repeated at follow-up (T1) using standardized procedures.

**Results:**

The study received ethics approval from the Clinical Research Ethics Committee of Aragón (PI21/278). Funding was provided by Instituto de Salud Carlos III through project PI22/01070 (cofunded by the European Union) for the period 2023-2027. Baseline assessments (T0) were initiated in late 2022/early 2023. As of February 2026, a total of 200 participants have been enrolled (n=100 Long COVID; n=100 recovered controls) and have completed T0; T1 assessments are scheduled for late 2025/early 2026 (~3-year follow-up for the earliest enrolled participants). Primary analyses will be conducted after completion of T1 assessments, with dissemination planned from the second half of 2026 and continuing through 2027.

**Conclusions:**

This protocol describes a comprehensive, multidimensional longitudinal study designed to clarify determinants of Long COVID by integrating clinical, functional, lifestyle, and immunobiological data in matched cohorts. Findings are expected to support risk stratification, phenotype discovery, and identification of prognostic markers to inform preventive, diagnostic, and rehabilitative strategies.

**Trial Registration:**

ISRCTN Registry ISRCTN27312680; https://tinyurl.com/33cbysrk

**International Registered Report Identifier (IRRID):**

DERR1-10.2196/67133

## Introduction

### Overview

The COVID-19 pandemic has substantially reshaped the global health burden by producing not only acute morbidity and mortality but also a spectrum of persistent postinfectious sequelae that continue to affect large numbers of survivors [1-3]. One of the most clinically and socioeconomically consequential of these sequelae is Long COVID, frequently termed postacute sequelae of SARS-CoV-2 infection (PASC), a heterogeneous syndrome comprising persistent, relapsing, or newly emergent symptoms after the acute phase of infection [4-6]. Population and cohort analyses show appreciable heterogeneity in estimates of prevalence across definitions, follow-up intervals, and dominant variants, with many studies reporting persistent symptoms in the approximate 10%-30% range among infected persons depending on case definition and follow-up timing [7-9]. Typical symptom clusters include debilitating fatigue, dyspnea/exertional intolerance, and cognitive dysfunction (often described as “brain fog”), and these complaints occur in individuals across the spectrum of acute disease severity, including those who had mild acute illness [2,8,9].

Mechanistic concepts for PASC are multifactorial and emphasize an interplay of viral, immune, and host-environment factors, including potential viral persistence or residual antigen, dysregulated or protracted immune activation, chronic systemic and tissue-specific inflammation, perturbations of metabolic pathways, and, in some patients, autoimmune sequelae [5,10,11]. Proteomic and metabolomic studies and longitudinal immune profiling have reported persistent alterations in circulating proteins and immune mediators—including reported associations with proinflammatory cytokines such as interleukin-6 (IL-6) and tumor necrosis factor-α—although results vary across cohorts and time points [10,12,13]. At the same time, psychosocial determinants (eg, preexisting psychiatric morbidity, chronic stress, and social isolation) and baseline comorbidity burden (eg, obesity, cardiopulmonary disease, and chronic kidney disease) have been associated with greater acute severity and may influence recovery trajectories, symptom perception, and care seeking after SARS-CoV-2 infection [14-17].

Despite rapid expansion of descriptive and mechanistic work, the extant literature remains fragmented: many investigations target single domains (immunologic, imaging, symptom inventories, or psychosocial measures) or selected subpopulations (hospitalized cases, clinic-referred patients, or pediatric cohorts), limiting integrative inference and generalizability [5,18]. Large electronic health record–driven and population-based studies have mapped cooccurrence patterns and identified candidate risk factors, but frequently lack prospectively collected multimodal biomarker and psychosocial data required to link biological signals to clinically meaningful longitudinal trajectories [6,19]. Neurocognitive sequelae exemplify this gap: observational and translational work implicates persistent neuroinflammation and systemic immune perturbations as plausible contributors to post–COVID-19 cognitive complaints and to accelerated decline among susceptible individuals, but definitive, integrative longitudinal evidence is limited [20-22]. Taken together, these observations emphasize the need for prospective, multimodal cohorts that combine standardized clinical phenotyping, serial biosampling, and structured psychosocial measurement to permit hypothesis-driven biomarker discovery and etiologic modeling of PASC [3,23].

Demographic factors and baseline comorbidities modulate both acute disease course and postacute outcomes: older age and multimorbidity are consistently associated with a higher risk of persistent symptoms and adverse long-term outcomes in many cohort studies, and prior cognitive impairment has been identified as a vulnerability factor for prolonged neuropsychiatric sequelae [9,24-26]. Obesity and chronic respiratory disease have been linked to greater acute severity and higher likelihood of prolonged symptoms, and these associations have implications for targeted surveillance and rehabilitation strategies [17,27,28]. Collectively, these epidemiologic and mechanistic observations underscore the need for health systems to develop evidence-based approaches to identify at-risk populations early and to tailor prevention, monitoring, and rehabilitation resources accordingly [3,23,29].

In summary, although the body of research on Long COVID has expanded quickly, there remains an urgent requirement for coordinated, integrative studies that synthesize clinical phenotyping, longitudinal immunology, objective physiologic assessment, and psychosocial characterization, with the ultimate goal of deriving reproducible biomarkers, mechanism-informed subtypes, and actionable interventions for PASC [3,5,6,12,23].

### Hypothesis and Rationale

We hypothesize that antecedent and periacute factors (eg, sociodemographic, preinfection comorbidities, and acute COVID-19 severity indicators) are associated with Long COVID status, and that baseline postacute measures collected at T0 (eg, patient-reported outcome measures and biochemical/immunological markers) primarily differentiate Long COVID from recovered controls as concurrent phenotypic correlates rather than implying causality. By comparing individuals with Long COVID to carefully matched recovered controls and repeating standardized assessments longitudinally, we aim to identify differential factors across clinical, immunological, and lifestyle domains. These findings are expected to support biomarker discovery, mechanism-informed subtyping, and clinically actionable risk stratification in future studies.

### Study Objectives

#### Primary Objective

The primary objective is to estimate associations between antecedent/periacute clinical and sociodemographic factors and Long COVID status, and to characterize postacute T0 clinical, biomarker, and psychosocial profiles as phenotypic differentiators between cases and matched recovered controls.

#### Secondary Objectives

The secondary objectives are as follows:

To characterize the Long COVID cohort with respect to demographics, comorbidity burden, and lifestyle habits.To evaluate associations between lifestyle factors and preexisting conditions and the presence and severity of persistent symptoms and functional impairment.To examine longitudinal change in symptoms and patient-reported outcomes between T0 and T1 within each group and compare trajectories between groups.

This protocol therefore describes a longitudinal matched case-control study designed to integrate clinical, functional, lifestyle, and immunobiological data to better understand determinants of persistent post–COVID-19 symptoms.

## Methods

### Study Design

This study is a longitudinal matched case-control study design combining a retrospective cohort with a prospective cohort. The retrospective cohort comprises individuals diagnosed during the early stages of the pandemic and provides long-term follow-up. In parallel, the prospective cohort will enroll newly identified COVID-19 cases, with follow-up assessments conducted after the baseline evaluation. This combined approach allows examination of symptom persistence for up to 3 years in the retrospective cohort while also enabling real-time tracking of changes over time in the prospectively enrolled participants. The study is registered in the International Standard Randomized Controlled Trial Number (ISRCTN) Registry (ISRCTN27312680), and reporting will adhere to the STROBE (Strengthening the Reporting of Observational Studies in Epidemiology) guidelines.

### Study Setting and Population

The study will be conducted in Aragón, Spain, leveraging the region’s established primary care network and health care infrastructure. Eligible participants will be adults (≥18 years of age) with a confirmed diagnosis of COVID-19. Participants will be identified through three complementary sources: (1) the Long COVID Aragón Patient Association (patients already registered with the association), (2) the Aragón Health Service database (individuals identified from electronic health records), and (3) primary care consultations (direct referrals from general practitioners and other health care professionals).

The Long COVID Aragón Patient Association is a regional, patient-led organization based in Aragón, Spain, that provides peer support, advocacy, and information for individuals experiencing persistent symptoms following SARS-CoV-2 infection. The association was established in 2020 in response to the emergence of postacute sequelae of COVID-19 and maintains a secure registry of members who voluntarily enroll and provide contact information and basic clinical descriptors (eg, date of acute infection, persistence and type of symptoms, and care pathways). Members who indicate willingness to be contacted for research constitute an important recruitment frame for this study, enabling identification of community-dwelling individuals with persistent symptoms who may not be fully captured through health care databases alone. For eligible individuals recruited through the association, study participation will proceed via the same standardized eligibility assessment and consent procedures used for all recruitment sources, and (where applicable and permitted) self-reported information will be verified or complemented using clinical records.

### Eligibility Criteria

Participants will be included if they have confirmed SARS-CoV-2 infection by polymerase chain reaction, antigen testing, or serology, and are aged ≥18 years. For the Long COVID group, eligibility will require persistence of symptoms for ≥12 weeks after infection onset, consistent with the World Health Organization (WHO) definition. For the control group, complete recovery will be defined as the absence of persistent or new symptoms after COVID-19. Individuals will be excluded if they refuse to participate, report preexisting symptoms similar to Long COVID prior to SARS-CoV-2 infection, or present severe psychiatric disorders or cognitive impairment that preclude informed participation.

### Sample Size Calculation

Because the primary aim of this study is hypothesis-generating—that is, to identify differential factors associated with Long COVID status rather than to test a single prespecified end point—sample size was chosen to provide adequate power to detect moderate associations between candidate predictors and case status within a matched case-control framework. Power was evaluated using the standard normal approximation for comparing 2 independent proportions (Fleiss et al [30]), with a 2-sided significance level of α=.05 and 90% power. Under a conservative scenario in which a candidate factor has an expected prevalence of 20% among controls, we considered an association of odds ratio 2.3 to be clinically meaningful; this corresponds to an expected prevalence of approximately 36.5% among cases. Under these assumptions, the required analyzable sample size is approximately 154 participants per group, rounded to 155 per group. To accommodate incomplete matching, potential attrition between T0 and T1, and planned multivariable and subgroup analyses, the overall recruitment target will be increased to approximately 400 participants [30].

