##### Objective 1 (Primary): Identify Factors Associated With Long COVID Status (Case vs Recovered Control)

Consistent with the study hypothesis that biopsychosocial characteristics, biomarkers, lifestyle factors, and comorbidities are associated with symptom persistence, the primary inferential analyses will model Long COVID status as the dependent variable.

As an initial descriptive step, we will summarize within-pair distributions and conduct paired comparisons as appropriate (eg, McNemar tests for binary variables; paired *t* tests, or Wilcoxon signed-rank tests for continuous variables). These comparisons will be used to describe patterns of differences and will not be used as the sole criterion for variable inclusion in multivariable models.

Adjusted associations with Long COVID status will be estimated using conditional logistic regression stratified by pair_id (matched sets), reporting adjusted odds ratios with 95% CIs. Model building will follow a prespecified, interpretable structure. A core adjustment set defined a priori will be included to address confounding not already controlled by matching (eg, acute disease severity indicators such as hospitalization/ICU admission where available, vaccination status/epoch if captured, and comorbidity burden). Candidate predictors will then be entered in clinically coherent blocks (eg, lifestyle/psychosocial block and biomarker block) to support interpretation of how associations change after adjustment for confounding and correlated predictors. Continuous predictors will be assessed for appropriate functional form (eg, linearity in the logit); flexible specifications (eg, splines) or clinically meaningful categories will be used when needed. Collinearity will be assessed (eg, variance inflation), and influential observations will be examined using standard diagnostics.

Biomarkers (routine laboratory tests, inflammatory markers including CRP and IL-6, cytokine panel, quantitative antispike immunoglobulin G, and viral reactivation serologies such as EBV/cytomegalovirus/HSV-1) will be treated as candidate correlates of Long COVID status. Continuous biomarkers will be summarized with appropriate transformations if skewed (eg, log transformation), and extreme values will be checked for plausibility and laboratory flags prior to analysis.

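### The 155 per group and 90% power come from an unmatched formula with the pairing assumption unstated, and the 20% prevalence labelled conservative is favourable for any rarer factor

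*Protocol article*

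**What the plan says.** All sizing inputs are in the protocol article, Sample Size Calculation. The section presents the power as applying to a matched case-control framework, but the method is for unmatched groups: "Power was evaluated using the standard normal approximation for comparing 2 independent proportions", "with a 2-sided significance level of α=.05 and 90% power". The inputs are a control prevalence ("Under a conservative scenario in which a candidate factor has an expected prevalence of 20% among controls") and an effect size ("we considered an association of odds ratio 2.3 to be clinically meaningful"), converted as follows: "this corresponds to an expected prevalence of approximately 36.5% among cases". The result is that "the required analyzable sample size is approximately 154 participants per group, rounded to 155 per group". To allow for incomplete matching, attrition, and multivariable and subgroup work, "the overall recruitment target will be increased to approximately 400 participants".

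Matching Strategy fixes individual 1:1 matching on sex/gender, age and diagnosis date. The primary analysis, under Objective 1, is paired: "Adjusted associations with Long COVID status will be estimated using conditional logistic regression stratified by pair_id (matched sets"). Planned Reporting of Findings repeats this. Recruitment and Follow-up Progress again presents 155 per group as the minimum analysable size for the matched framework.

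**The concern.** For a single binary factor, conditional logistic regression on 1:1 pairs uses only the pairs in which case and control differ in exposure, and it estimates a conditional odds ratio. Its power depends on the proportion of discordant pairs, and so on how strongly exposure is correlated within pairs. The sizing section is silent on both. The 90% is therefore not derived for the planned test, although it is presented as if it were.

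The second problem does not depend on pairing. Calling 20% prevalence conservative tells the reader that other candidate factors will be at least as well powered. At a fixed odds ratio of 2.3 that is true for commoner factors and false for rarer ones. The primary objective concerns antecedent and periacute factors such as comorbidities, hospitalization and ICU admission. A reader who trusts the label could take a null result for a rare factor as evidence against an association of the size the protocol calls meaningful.

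**Working it through.** **Inputs.** From Sample Size Calculation: two-sided alpha 0.05 (z = 1.960), power 90% (z = 1.2816), control prevalence p0 = 0.20, odds ratio 2.3. Assumed, because the protocol gives no value: phi = 0, 0.1, 0.2.

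**Step 1. Reproduce the plan's figure.**

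p1 = 2.3 × 0.20 / (0.80 + 2.3 × 0.20) = 0.46 / 1.26 = 0.3651, which agrees with the stated 36.5%.

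With q = 1 − p and p̄ = (0.20 + 0.3651)/2 = 0.2825, the uncorrected two-proportion formula is

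n = [1.960·√(2p̄q̄) + 1.2816·√(p0q0 + p1q1)]² / (p1 − p0)²

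= [1.960 × 0.6367 + 1.2816 × 0.6259]² / 0.1651² = 154.2.

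This rounds up to 155, where power is 90.1%. The stated figure is right for the method named.

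**Step 2. The paired requirement.**

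Let c = phi·√(p1q1p0q0). The discordant-pair probabilities are p10 = p1(1 − p0) − c (case exposed only) and p01 = (1 − p1)p0 − c (control exposed only). With pd = p10 + p01 and d = p10 − p01, the McNemar sample size is

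N = [1.960·√pd + 1.2816·√(pd − d²)]² / d².

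At phi 0: p10 = 0.2921, p01 = 0.1270, pd = 0.4190, d = 0.1651, so N = 157.4, or 158 pairs.

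For phi above 0 the answer depends on what is held fixed. Either the conditional odds ratio p10/p01 stays at 2.3 and the case prevalence is re-solved, or the stated 20% and 36.5% stay and the conditional odds ratio moves.

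| Held fixed | phi | Case prevalence | p10 / p01 | Conditional OR | Pairs for 90% | Power, 155 pairs | Power, 200 pairs |
|---|---|---|---|---|---|---|---|
| both readings coincide | 0 | 36.5% | 0.2921 / 0.1270 | 2.30 | 158 | 90% | 96% |
| conditional OR 2.3 | 0.1 | 34.5% | 0.2573 / 0.1119 | 2.30 | 180 | 85% | 93% |
| conditional OR 2.3 | 0.2 | 32.6% | 0.2236 / 0.0972 | 2.30 | 207 | 80% | 89% |
| 20% vs 36.5% | 0.1 | 36.5% | 0.2728 / 0.1077 | 2.53 | 143 | 92% | 97% |
| 20% vs 36.5% | 0.2 | 36.5% | 0.2535 / 0.0885 | 2.87 | 128 | 95% | 98% |

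The 200 pairs are the full target of about 400 split equally with no pair lost, so they are an upper bound.

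**Step 3. Prevalence, with the plan's own unmatched formula at odds ratio 2.3.**

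| Control prevalence | Case prevalence | n per group for 90% | Power at 155 | Power at 200 |
|---|---|---|---|---|
| 5% | 10.8% | 453 | 47% | 58% |
| 10% | 20.4% | 251 | 72% | 82.5% |
| 15% | 28.9% | 185 | 84% | 92% |
| 20% | 36.5% | 155 | 90% | 96% |
| 30% | 49.6% | 129 | 95% | 98% |
| 40% | 60.5% | 123 | 95% | 99% |

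The requirement is lowest near 40% and rises steeply below 20%.

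Both steps treat one binary factor without covariates. The adjusted model and the continuous scores and biomarkers are not covered by these figures, nor by the protocol's own calculation.

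**The case against.** The best defence on pairing is that the protocol states both prevalences, and its conversion of 2.3 into 36.5% is the marginal one. If those prevalences are held, positive within-pair correlation lowers the requirement and 155 is more than enough. At phi 0 the two formulas differ by only about three pairs. This stands. A reader might infer that ignoring the matching leaves the study too small, and the document does not support that: phi is not given, and the direction depends on an unstated choice. What remains is that the planned model reports a conditional odds ratio and the section never says which one 2.3 is.

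The target of about 400 also softens the matter. With all 200 pairs intact, power at 20% prevalence is still 89% on the less favourable reading at phi 0.2. But the extra recruitment is assigned to incomplete matching, attrition, and multivariable and subgroup analyses, and even all of it gives only 82.5% at 10% prevalence and 58% at 5%.

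On the label, 20% is indeed conservative against commoner factors, many candidates are continuous, and no prevalence is given for hospitalization, ICU admission or any comorbidity. A reader might infer that these are in fact rarer than 20%, but the document cannot show it. Equally, it offers nothing to show that they are not, which the label requires.

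The declared hypothesis-generating aim lowers the stakes, but a specific power figure is still claimed. The Limitations section concedes low power for rare outcomes and for fine subgroups. It does not mention rare exposures, which are the issue here because case status is fixed 1:1 by design.

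**Conclusion.** The point holds in two parts.

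First, the 90% power is stated for a matched framework but derived for an unmatched one, without the assumption that would link the two. The arithmetic is correct for the formula named. Over an assumed phi of 0 to 0.2, the paired requirement runs from 128 to 207 pairs around the stated 155, and power at 155 pairs runs from 80% to 95%. This is an unstated assumption with an effect in either direction, not a demonstrated shortfall.

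Second, 20% is not a conservative prevalence for a study that screens many factors. This part needs no assumption about phi. At odds ratio 2.3, power at 155 per group is 84% at 15% prevalence, 72% at 10% and 47% at 5%. Whether particular listed factors are that rare is an assumption.

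Neither part concerns how many participants have been enrolled so far, which is a separate matter.

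**What to change.** Rewrite the paragraph in Sample Size Calculation:

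- Recompute with the discordant-pair (McNemar or conditional) formula.
- State whether the odds ratio of 2.3 is conditional or marginal.
- Show the result for phi from 0 to 0.2, labelled as an assumed range.
- Delete the word *conservative*.
- Report power or the detectable odds ratio at 5%, 10% and 20% control prevalence, for 155 pairs, for up to 200 pairs, and for the number of pairs actually analysed.
- Carry the revised figure into Recruitment and Follow-up Progress, and name rare exposures in Limitations.

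The cost is one recalculated paragraph and two small consequential edits. The stated power becomes less favourable for rarer factors. At 20% prevalence it may move either way, depending on which odds ratio is meant. No new participants and no change to the analysis are needed.
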